**Figure 2 F2:**
[figure not shown]
Indicative map of the TARS intervention components. TARS, Trial of physical Activity-assisted Reduction of Smoking.

Participants allocated to the intervention arm were offered individually tailored behavioural support from a health trainer. The health trainer delivered the processes outlined in figure 2 and table 2, with the option of up to eight weekly sessions, and a further six sessions if the participant wanted support after quitting, and aimed to empower participants to decide what support was offered, and where, when and for how long. Signposting to local smoking cessation support services was also offered to those wishing to quit. If a smoker wished to reduce smoking using e-cigarettes or licensed nicotine-containing products (LNCP), they were also offered any local available support for this.

Health trainers were appointed on the basis of having good communication skills, including empathy, and at least some training and experience in supporting health behaviour change. All health trainers had at least a first degree in a related field although this was not a prerequisite for the role. The health trainer was trained to support change in both smoking and PA and help individuals to make the connections between the two. As described in table 2, the core intervention processes that the health trainer was trained to deliver were: (1) building rapport and supporting autonomous behaviour change; (2) building motivation; (3) supporting self-monitoring and goal setting; (4) problem solving; (5) integrating smoking and PA behaviour; (6) supporting a health identity shift; (7) supporting the management of social influence on behaviours.

The support offered was broadly structured (based on delivering the processes outlined in table 2 and figure 2) but health trainers were trained to be flexible in their approach, to tailor it for individual needs and preferences. They were trained to do this using a person-centred approach and principles from motivational interviewing such as showing empathy and reflective listening.^36^ They were also trained to assess (and be aware of) participants’ needs in relation to the core psychological needs posited by Self-Determination Theory,^37^ which we referred to in the training as ‘the three Cs’: Control (having choice/autonomy in decision-making around behaviour change); Competence (developing self-efficacy/building confidence in the ability to change) and Connectedness (social acceptance of the new behaviour/support from important others for making changes).

A fuller intervention description, including the trainer manual and intervention materials, will be published as supplemental materials linked to the final National Institute for Health Research project report.

#### Support as usual

Participants allocated to both arms of the trial received written guidance for smoking reduction and cessation, including web links to what is offered at local level, or paper versions of this information. Typically, there are no formal programmes for use of medication to support reduction (rather than abrupt stopping) and people usually buy their own replacement therapy or e-cigarette product.

### Determination of sample size

Since the planned primary analysis is a comparison of the proportions of the binary primary outcome, the sample size calculation was based on a two-sided Fisher exact test. An abstinence rate of 5% for the control group and detectable effect of 6% (ie, an increase from 5% to 11% due to the intervention) are conservative estimates consistent with those from the EARS pilot study^15^ and those reported from a systematic review of pharmacological interventions.^38^ The corresponding OR for this effect size is 2.35. Participants with missing outcome data will be assumed to be still smoking following the Russell Standard,^39^ and the numbers of participants in each allocated group are assumed to be in the ratio of 1:1. Under these conditions, according to Stata V.14.2, the minimum number of participants required to detect an abstinence rate of 11% compared with that of 5% in the control group, with a significance level of no more than 5% and power of at least 90%, is 900, above which a power in excess of 90% is maintained.

### Outcome measures

Table 1 lists the outcome measures and when they are being assessed.

#### Primary outcome measure

Biochemically verified 6-month floating prolonged abstinence between 3 and 9 months.^40^ Abstinence will be confirmed by expired CO <10 ppm measured with a CareFusion MicroCO metre (Williams Medical Supplies, Rhymney, UK, www.carefusion.co.uk) at a face-to-face visit.

Participants who self-reported abstinence at 3 months and who were confirmed as abstinent through biochemical verification via expired CO at a face-to-face assessment and then self-report abstinence (and not having smoked even a puff since the 3-month assessment) at 9 months, again confirmed by expired CO, will be defined as having prolonged abstinence over at least 6 months.

#### Other smoking-related measures

Only participants who have biochemically verified abstinence at 9 months are being contacted at 15 months post-baseline to assess floating prolonged abstinence over a period of 12 months (3–15 months). Participants who were not abstinent at 3 months but have biochemically confirmed abstinence at 9 months will be contacted at 15 months to confirm floating prolonged abstinence of 6 months between 9 and 15 months. As a contingency measure for verification of abstinence during the COVID-19 outbreak, abstinence will be confirmed by saliva cotinine level <12 ng/mL^41^ using a mailed self-collection kit and assay provided by ABS Laboratories (York, UK, www.acmgloballab.com). This contingency measure will apply to follow-up for secondary outcomes for a minority of participants. While the intervention is expected to primarily influence quitting in the first 3 months of the study, it is possible that a sustained quit attempt occurs after the 3-month assessment as a result of the health trainer building behaviour change skills which are used subsequently to reduce and then quit smoking.

Participants are asked to self-report the number of cigarettes smoked and type of nicotine product (ie, pipes, cigars and roll your own). We estimated 0.45 g of tobacco was the equivalent of one cigarette based on a previous rigorous study^42^ and reported in the EARS pilot study.^15^ From this we will estimate the number of cigarettes smoked at follow-up, and also calculate if participants reduce smoking by at least 50% between (1) baseline and 3 months, and (2) baseline and 9 months.

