### Study population

Potential participants were approached from primary and secondary care establishments and also from the community. Participants were adult smokers (≥18 years) who smoked ≥10 cigarettes per day (for at least 1 year), wished to reduce smoking but not quit immediately. We accepted smokers who were also using other nicotine-containing or other cigarette management products. Smokers were ineligible if they were unable to engage in at least 15 min of moderate intensity PA, had any illness or injury that might be exacerbated by exercise, were unable to engage in the study and/or the intervention due to language or for other reasons (eg, provide an unacceptable level of risk to the health trainer or researcher). All ineligible smokers were referred for smoking cessation advice in line with local usual practice.

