#### Analysis of secondary outcomes

Between-group comparisons will be undertaken, including for the following key secondary outcomes:

Biochemically verified point prevalence abstinence at 3, 9 and 15* months post-baseline.Self-reported point prevalence abstinence at 3, 9 and 15* months post-baseline.Prolonged biochemically verified abstinence over 6 months between 9 and 15 months post-baseline.Prolonged biochemically verified abstinence for at least 12 months between 3 and 15 months post-baseline (derived from biochemically confirmed abstinence at all three follow-up time points).At least a 50% reduction in reported smoking levels between (1) baseline and 3 months, and (2) baseline and 9 months.Number of cigarettes used on an average day over the past week (including equivalent cigars, tobacco) at 3, 9 and 15* months post-baseline.Total number of LNCP used on an average day over the past week at 3, 9 and 15* months post-baseline.Total number of self-reported minutes engaged in MVPA over the past week at 3 and 9 months post-baseline.BMI at 3 and 9 months post-baseline.

NB: * only for those with biochemically confirmed abstinence at 9 months.

The following data are derived from accelerometers mailed to a subgroup of participants in both arms of the trial along with the 3-month questionnaire, which are returned after the accelerometers have been worn for 7 days:

The average time spent in moderate to vigorous activity over the past week.The average daily time spent sleeping over the past week.

No adjustment for multiple analyses will be made; such adjustment methods are too conservative when outcomes are positively correlated, as they would be in this trial. Analyses will use multivariable linear regression (continuous outcomes) or logistic regression (binary outcomes) to compare each of these secondary outcomes between allocated groups, with adjustment for site as a factor, and HSI, as an ordinal variable, as well as baseline values of the outcome as appropriate. As accelerometer data were only available at 3 months, only summary statistics for weekly minutes of MVPA shall be presented by allocated group without adjustment for baseline variables.

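### Under the COVID-19 contingency, saliva cotinine can fail smoke-free users of nicotine products, so the verified 15-month outcomes mix two definitions of abstinence

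*Protocol article*

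**What the plan says.** For the primary outcome the protocol article (Primary outcome measure) sets the rule "Abstinence will be confirmed by expired CO <10 ppm", measured face to face. Under Other smoking-related measures it gives a substitute for the outbreak: "abstinence will be confirmed by saliva cotinine level <12 ng/mL", from a mailed self-collection kit. The scope is limited: "This contingency measure will apply to follow-up for secondary outcomes for a minority of participants". The substitute appears in the paragraph on 15-month contact, so I read it as applying to that assessment. Only participants with verified abstinence at 9 months are contacted then.

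The article expects nicotine products to be in use:

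- Study population: "We accepted smokers who were also using other nicotine-containing or other cigarette management products".
- Intervention: "If a smoker wished to reduce smoking using e-cigarettes or licensed nicotine-containing products (LNCP), they were also offered any local available support for this".
- Support as usual: "people usually buy their own replacement therapy or e-cigarette product".

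Three secondary outcomes need verification at 15 months: point prevalence, prolonged abstinence from 9 to 15 months, and prolonged abstinence from 3 to 15 months. The last is "derived from biochemically confirmed abstinence at all three follow-up time points". Table 1 records use of smoking management products at month 15.

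**The concern.** Expired CO is a marker of smoke. Cotinine is a metabolite of nicotine, whatever its source. This is general pharmacology and is not stated in the article. The two tests agree for an abstainer who uses no nicotine, but can disagree for one who uses nicotine replacement or a nicotine e-cigarette.

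The trial's endpoint is abstinence from smoking, not from nicotine. Applied as written, the contingency can withhold confirmation from someone who has not smoked and who passed CO twice. Two participants with identical behaviour could be classified differently only because one reached 15 months during the outbreak.

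The verified 15-month outcomes are at stake, including prolonged abstinence at 15 months, which is one of the trial's specific aims. Events are few, because only verified 9-month abstainers are followed, so each misclassification counts.

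**Working it through.** **Rules side by side.** Take a participant who has not smoked since before month 3 and uses a nicotine e-cigarette throughout.

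- CO at 3, 9 and 15 months: can be confirmed each time, and counts as abstinent from 3 to 15 months.
- CO at 3 and 9 months, cotinine at 15 months: can read 12 ng/mL or above, is then not confirmed at 15 months, and drops out of all three verified 15-month outcomes.

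**The plan's own figures.** The sample size section gives 5% versus 11%, an odds ratio of 2.35 and a total of 900. The odds ratio is (0.11/0.89)/(0.05/0.95) = 2.348, which agrees. Full enumeration of the two-sided Fisher exact test gives power 0.8995 at 449 per arm and 0.9003 at 450 per arm, so 900 is reproduced. The point does not depend on these figures; they only give a scale.

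**Size of the loss.** Let c be the share of true 15-month abstainers verified by cotinine, and u the share of them using nicotine products. The article gives neither. I assume c = 10% to 40% and u = 20% to 60%, that use is unrelated to verification method, and, as a worst case, that every user reads 12 ng/mL or above.

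Fraction lost = c × u; observed rate = true rate × (1 − c × u).

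For illustration, take 450 per arm and true 15-month rates equal to the design rates, 5% and 11%. That is 22.5 and 49.5 abstainers.

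| c | u (both arms) | Lost | Observed rates | Abstainers lost (control, intervention) | OR |
|---|---|---|---|---|---|
| 10% | 20% | 2% | 4.90% vs 10.78% | 0.45, 0.99 | 2.34 |
| 25% | 40% | 10% | 4.50% vs 9.90% | 2.25, 4.95 | 2.33 |
| 40% | 60% | 24% | 3.80% vs 8.36% | 5.40, 11.88 | 2.31 |

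Normal-approximation power in these three rows is 0.908, 0.881 and 0.818, against 0.914 with no loss.

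With lower assumed rates of 3.5% and 7.7% (the design rates × 0.7), c = 35% and u = 30% in both arms, the loss is 0.35 × 0.30 = 10.5%. Observed rates are 3.13% and 6.89%, and the odds ratio goes from 2.30 to 2.29.

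**Unequal product use**, with c = 40% and true rates of 5% and 11%:

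- u = 20% control, 60% intervention: 0.05 × 0.92 = 4.60% and 0.11 × 0.76 = 8.36%; odds ratio 1.89.
- u = 60% control, 20% intervention: 0.05 × 0.76 = 3.80% and 0.11 × 0.92 = 10.12%; odds ratio 2.85.

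**The case against.** The strongest objection is that this is a condensed article. It says that it summarises the main analyses and that a detailed analysis plan exists, and a rule for nicotine-product users may sit there or in an amendment. That is possible, and quoting such a rule would close the point. But the article does more than leave a detail out: it states a working rule with a cut-off, and that rule as written can misclassify a group the trial chose to enrol.

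A second objection is that failing towards smoker is conservative and matches the handling of missing data. That is fair for the abstinence rate within an arm. It does not protect the comparison, because the bias can go either way if product use differs between arms.

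A third is that accepting self-report would abandon biochemical verification in a trial whose participants know their allocation. This stands as an objection to making self-report the only analysis, and the fix below allows for it.

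A reader might infer that every quitter on nicotine replacement or e-cigarettes is scored as a smoker at 15 months, and that the intervention effect is therefore understated. The article does not support that. CO-verified participants are untouched. Light users, or users of nicotine-free products, may read below 12 ng/mL. Nothing shows greater product use in the intervention arm: health trainers offered access to product support, but both arms received guidance on local support, and under usual support people commonly buy such products themselves.

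**Conclusion.** The point holds in a limited form. For the minority verified by cotinine, the stated rule can fail smoke-free users of nicotine products. Verified point prevalence at 15 months and prolonged abstinence over 9 to 15 and 3 to 15 months then combine a smoke-free with a nicotine-free definition and can under-count abstainers. The CO-based primary outcome and self-reported 15-month abstinence are not affected.

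The size cannot be fixed from the article. The 2% to 24% loss rests entirely on the assumed ranges for c and u and on the worst case that every product user fails. With equal use in the two arms the odds ratio is nearly unchanged (2.35 to 2.31 at the extreme). With unequal use it could fall to about 1.89 or rise to about 2.85 in the cases shown, and the direction is unknown. This is a modest fault in secondary outcomes that is cheap to correct.

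**What to change.** Before database lock, add to the analysis plan:

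1. A cotinine reading of 12 ng/mL or above in a participant who reports nicotine-product use at 15 months is not by itself evidence of smoking, and is treated as not verifiable by cotinine.
2. Each verified 15-month outcome is analysed twice: with these participants counted as smokers, and with them counted as abstinent on self-report.
3. The number verified by each method, with reported product use, is given by arm.

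Table 1 already collects product use at month 15, so no new data are needed. The cost is some wording and one extra analysis per outcome. The small downside is that in one of the two analyses a few participants rest on unblinded self-report; the other analysis bounds the effect of that.

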#### PA measures

The 7-day recall measure of PA^43^ is used to assess self-reported weekly minutes of moderate and vigorous PA. An objective measure of total weekly minutes of moderate and vigorous PA (MVPA) was collected with a wrist-worn waterproof GENEActiv accelerometer^44^ around the 3-month follow-up time point. Participants were asked to wear the accelerometer on the wrist of the non-dominant hand constantly for 1 week and then return to the CTU. This accelerometer shows the wearer no information about their PA levels and does not have obvious motivational value.

#### Physical measures

Participants are asked to self-report their height and weight from which body mass index (BMI) will be calculated.

#### Health-related quality of life measures

The EuroQol-5 dimension-5 level (EQ-5D-5L) (EuroQol Group, 1990) comprises the following five dimensions: mobility, self-care, usual activities, pain/discomfort and anxiety/depression. Each dimension has five levels: no problems, slight problems, moderate problems, severe problems and extreme problems.^45^ The 12-Item Short Form Health Survey is a 12-item, patient-reported survey of patient health, consisting of 12 questions.^46^

#### Resource use/healthcare service use

Use of primary and community-based health and social services, and hospital-based inpatient and outpatient services are captured using a resource use questionnaire developed in two pilot trials involving health trainer-led interventions.^16 47^ It sought to capture the number of contacts that occurred (if any) with a range of health and social care professionals and where those contacts took place since completing the previous survey, using both fixed and open format responses. Reasons for hospital admissions were also requested.

#### Self-reported process measures

Single-survey items, using a 5-point Likert scale (strongly disagree to strongly agree) assessed the psychological and behavioural processes that the intervention was designed to influence as shown in table 2. These were used in other trials.^15 48 49^ A single-survey item, using a 6-point scale (not at all to all the time), was used to assess frequency of urge to smoke in the past week.^50^ A single survey item (6-point Likert scale, no urges to extremely strong) assessed strength of urges to smoking in the past week^50^ as used previously.^15^

### Economic evaluation

The economic evaluation will (1) estimate the long-term cost-effectiveness of the TARS intervention plus SAU versus SAU alone, over a lifetime horizon using a model-based economic evaluation, and (2) estimate the cost-effectiveness of the TARS intervention plus SAU versus SAU alone over the primary 9-month trial follow-up, in an economic evaluation conducted alongside the trial. The longer term model-based economic analysis is considered the primary economic analysis, consistent with the approach commonly applied in the context of cost-effectiveness analysis in smoking cessation settings.

The primary perspective of the economic analyses will be that of the NHS and Personal Social Services (ie, third party payer), with a broader perspective explored in sensitivity analyses. The primary economic endpoint will be the quality-adjusted life-year (QALY, using EQ-5D data), with results presented as incremental cost-effectiveness ratios representing estimated costs per QALY gained.

The economic analysis will be undertaken against a predefined health economics analysis plan, which is available on request. In summary, the trial-based cost-effectiveness analysis will use participant-level data collected within-trial to estimate (1) the resource use and costs associated with the delivery of the TARS intervention, (2) broader resource use and costs associated with health and care service use by group, (3) QALYs by group, and (4) the incremental cost per unit of outcome (eg, cost per incremental QALY, cost per quitter) over the 9-month follow-up. In this analysis, EQ-5D-5L data will be used to estimate QALYS, deriving health state values at each time point, using the published tariff values for England (presently recommendations are for values to be derived using methods reported by van Hout *et al)*,^51^ and using the area under the curve approach.^52^ Analyses will be based on an intention-to-treat (ITT) principle, using a complete case analysis, and will assess uncertainty and include detailed sensitivity analyses.

The model-based economic evaluation will adopt a longer term perspective (lifetime) beyond the trial follow-up, to present a policy relevant cost-effectiveness analyses, that predicts future costs and QALYs after the trial endpoint based on the reported effectiveness of the TARS intervention. A decision analytic model will be used, with the model based on the model developed and described in the prior pilot study (EARS),^15^ which we will update and adapt using a review of the recent literature on modelling in this area and based on input from a stakeholder group. The model-based evaluation will be based on good practice guidelines for decision analytic modelling in the health technology assessment context.^53–55^

### Embedded mixed-methods process evaluation

A mixed-methods process evaluation will focus on trial processes and methods, and will attempt to understand the effective components and processes of the intervention. During the internal pilot phase, the evaluation will focus on barriers and facilitators for recruitment methods, initial intervention engagement and early intervention implementation. For the subsequent main trial, the evaluation will focus on acceptability of study processes (via a qualitative substudy), intervention engagement levels, predictors of intervention engagement, intervention delivery fidelity and evaluating the implementation of the intervention process model (participant understanding of the intervention model (receipt fidelity), mediating effects of process measures on PA and smoking outcomes (enactment fidelity), mediating effects of PA on smoking outcomes, approaches and acceptability of smoking reduction, multiple behaviour change, progression to cessation and other perceived effectual intervention components).

Data for the process evaluation will be collected via: the trial database, audio recordings of intervention sessions, and audio recorded and transcribed interviews with trial participants, research assistants, health trainers and GPs/practice managers.

